## Abstract

**Background:**

Neovascular age-related macular degeneration (nAMD) is the most common cause of irreversible vision loss and blindness among the older people aged 50 and over. Although anti-vascular endothelial growth factor (anti-VEGF) therapies have resulted in improving patient outcomes, there are limitations associated with these treatments. In China, traditional Chinese medicine (TCM) has been used to treat eye diseases for more than 2000 years. Previous studies have shown that TCM may be beneficial for nAMD patients. However, explicit evidence has not been obtained. The purpose of the present trial is to examine the efficacy and safety of the Mingjing granule, a compound Chinese herbal medicine, for nAMD patients.

**Methods/design:**

This is a double-blind, placebo-controlled, randomized trial of Mingjing granule as an add-on to intravitreous ranibizumab for nAMD. One hundred eighty nAMD patients from six hospitals in China will be enrolled according to the inclusion and exclusion criteria and randomly allocated into two groups, 90 in each. All participants will receive a 24-week treatment and then be followed up for another 24 weeks. The primary outcome is the mean change of best-corrected visual acuity at week 24 and 48 as compared to the baseline. The secondary outcomes include mean change in central retinal thickness, area of retinal hemorrhage and exudation, and TCM syndrome score, mean number of intravitreal ranibizumab injection, and total cost of the treatment. Indexes of safety include blood regular test, urine regular test, liver function test, renal function test, and electrocardiogram from baseline to weeks 24 and 48. Qualitative control and some standard operating processes will be formed throughout the trial. Any ocular or systemic adverse events will be treated suitably, and related data will be recorded accurately and completely in the case report form.

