## Methods

### Trial design

This is a randomized, double-blind, placebo-controlled trial. Participants will be randomly allocated into two groups, the test group and the control group. Patients in the test group will receive Mingjing granule plus ranibizumab, while those in the control group will receive placebo with ranibizumab. All of them will be followed up every 4 weeks. Mingjing granule and placebo will be dispatched every 4 weeks until week 24; ranibizumab will be administered as needed after three consecutive monthly injections until week 48 (Figs. 1 and 2). The protocol is designed following the guidelines of the Consolidated Standards of Reporting Trials and Standard Protocol Items: Recommendations for Interventional Trials (SPIRIT) (see Additional file 1 SPIRIT 2013 checklist). The trial has been registered with the Chinese Clinical Trial Registry (ChiCTR2000035990, registered on 21 August 2020).

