## Outcomes

### Primary outcome

#### The mean change of BCVA (from baseline to weeks 24 and 48)

We will assess the participants’ best-corrected distance visual acuity by ETDRS charts before and after the treatment at weeks 24 and 48. When necessary, the participants will be examined more than once.

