#### Sample size

We design a superiority trial with a ratio of 1:1. The primary outcome is the mean change of BCVA at week 48 as compared to the baseline. After reviewing some literature, the mean change of BCVA in the test group is expected to increase by 10.1 letters measured by ETDRS chart, which in the control group is expected to increase by 8.2 letters [39, 40]. *n*_*c*_ is the participants’ number in each group. σ (standard deviation of the two groups) = 4. *Z*_1−*α*_ = 1.96, when *α* = 0.025; *Z*_1−β_ = 0.84, when *β* = 0.2. Δ = 0, *K* = 1, μ_T_ = 10.1, μ_C_ = 8.2. We calculate it by the PASS software; there are 71 cases in each group. Considering a 20% drop-out rate, there are 89 cases in each group and a total of 178 cases in both groups. Thus, we plan to recruit 180 participants in total (30 cases in every center, 15 cases in each group). The sample size calculation formula is as follows [41]:
$$ {n}_c=\frac{{\left({Z}_{1-\upalpha}+{Z}_{1-\upbeta}\right)}^2{\sigma}^2\left(1+1/K\right)}{{\left({\mu}_T-{\mu}_C-\Delta \right)}^2} $$

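### The protocol makes BCVA change primary at both week 24 and week 48 in two places, but at week 48 alone in the sample size section

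*Protocol article*

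**What the plan says.** Three statements define the primary outcome.

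- Abstract, Methods/design: "The primary outcome is the mean change of best-corrected visual acuity at week 24 and 48 as compared to the baseline".
- Outcomes, Primary outcome: the heading reads "The mean change of BCVA (from baseline to weeks 24 and 48", and the text beneath it has acuity assessed at both weeks.
- Sample size: "The primary outcome is the mean change of BCVA at week 48 as compared to the baseline".

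The Sample size section then builds a single comparison. It assumes a gain of 10.1 letters on test and 8.2 letters on control, and takes "σ (standard deviation of the two groups) = 4", with a Z of 1.96 "when *α* = 0.025" and 80% power. It arrives at 71 per group, 89 per group after 20% drop-out, 178 in total, and rounds to 180.

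The two weeks differ in what they measure. Trial design says that "Mingjing granule and placebo will be dispatched every 4 weeks until week 24", while as-needed ranibizumab continues to week 48. Statistical methods makes all tests one-sided with significance at P < 0.05 and does not mention the two weeks separately.

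**The concern.** The protocol fixes which outcome is primary, and here it fixes it in two incompatible ways. The choice matters because the weeks ask different questions. Week 24 measures the effect at the end of granule treatment. Week 48 measures what remains 24 weeks later, with ranibizumab given as needed in between. An effect could show at one and not at the other.

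If it did, the abstract and the Primary outcome section could support a claim of success on week 24 alone, while the Sample size section would call the same data a failure. A choice made once results are known cannot be shown to be independent of them. Depending on how two primary weeks were combined, the price is either a higher false-positive rate or lower power than planned.

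**Working it through.** **1. Reproduce the plan's sample size.** All inputs come from the Sample size section: difference 10.1 − 8.2 = 1.9 letters, SD 4, Z values 1.96 and 0.84, ratio 1:1, margin 0.

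n per group = 2 × (1.96 + 0.84)² × 4² / 1.9² = 2 × 7.84 × 16 / 3.61 = 69.5, so 70 by the printed normal formula. The t-based calculation gives 71, the stated figure (power 79.7% at 70 and 80.3% at 71). Drop-out: 71 / 0.8 = 88.75, so 89 per group and 178 in total. The plan's figures reproduce, for one comparison at one-sided 0.025.

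**2. If success at either week counted, with no adjustment.** Error = 1 − P(Z₁ < c and Z₂ < c), where Z₁ and Z₂ are bivariate normal with correlation ρ. ρ is not in the documents and is shown as a range.

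| ρ (assumed) | c = 1.96 (2.5% per test) | c = 1.645 (5% per test) |
|---|---|---|
| 0.5 | 4.5% | 8.8% |
| 0.7 | 4.2% | 8.0% |
| 0.9 | 3.5% | 6.8% |

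Each column should be read against its own single-test level. Multiplicity adds 1.0 to 2.0 percentage points to 2.5%, or 1.8 to 3.8 points to 5%.

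**3. If success at both weeks were required.** Error is not inflated, and the cost is power. Assume 80% power at each week; the week 24 figure is an assumption, since the protocol gives no effect or SD for that week. Joint power = P(Z₁ < 0.84 and Z₂ < 0.84):

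| ρ (assumed) | Joint power |
|---|---|
| 0.5 | 69% |
| 0.7 | 71% |
| 0.9 | 75% |

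If week 24 had about 92% power instead (also an assumption), joint power would be 76% at ρ = 0.5 and 80% at ρ = 0.9.

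**4. If week 48 is the only primary comparison.** Step 1 applies unchanged: 71 per group, 89 after drop-out, and the planned 180 covers the 178 required.

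**The case against.** The strongest defence is that week 48 was always the confirmatory time point and the other two places are loosely worded. The label naming both weeks is also attached to retinal thickness, haemorrhage and exudation, and the TCM score, so it may be only an assessment schedule. The Sample size section is the one place that ties the outcome to a hypothesis, an effect and an alpha, and it says week 48. This reading is plausible and supports the direction of the fix. It does not remove the conflict, because the abstract states outright that the primary outcome is the change at both weeks.

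A second defence is that a condensed article may leave the multiplicity rule to the full protocol or the analysis plan, neither of which is shown. That stands. The absence of an alpha split or joint rule is not a finding by itself, and a reader should not infer that the trial will test each week at the full level and accept either. The blanket sentence in Statistical methods is compatible with that but does not say it. An unseen plan cannot, however, agree with both definitions of the primary outcome.

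A reader might also set 6.8–8.8% against the 2.5% used for the sample size and attribute the whole gap to the two time points. That mixes two defects. Sample size uses one-sided 0.025 and Statistical methods one-sided 0.05, so a single time point already carries 5% under the latter. That discrepancy is a separate point.

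Finally, the loss of power is conditional. Week 24 is the end of treatment, where the effect could be larger, and the shortfall could then be small.

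**Conclusion.** The contradiction holds on the text alone: two places make weeks 24 and 48 primary, and one makes week 48 alone primary and sizes the trial for it. It governs the main conclusion of the trial and should be resolved before unblinding.

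The size of the harm depends on a decision rule that the protocol does not state. The two consequences are alternatives and cannot both occur:

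- Either week suffices: one-sided error of 3.5–4.5% instead of 2.5%, or 6.8–8.8% instead of 5%, for an assumed correlation of 0.5 to 0.9.
- Both weeks required: joint power of about 69–75% instead of 80%, for the same correlations and an assumed 80% power at week 24.

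A reader might infer that the trial is undersized. The documents do not support that: if week 48 is confirmed as the sole primary time point, the sample size stands.

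**What to change.** In the abstract and the Primary outcome section, name BCVA change at week 48 as the single primary time point, to match Sample size. Make week 24 the first secondary comparison, tested in fixed sequence only if week 48 is significant. Test both at the one-sided 0.025 used for the sample size. State that level explicitly, because under the 0.05 in Statistical methods the sequence would control error at 5%.

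If the sponsor prefers the end-of-treatment question, the order can be reversed. The Sample size section ties its 10.1 and 8.2 letters and SD of 4 to week 48, so those inputs must first be restated and justified for week 24 and the number of participants recalculated.

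With week 48 first, the change is to wording only. It needs no more participants and no split of alpha. The downside is that a win at the second-ranked week alone no longer counts as primary success. The registry entry and any analysis plan are not visible here; they should be checked for the same definition and aligned if they differ.

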**Discussion:**

Based on previous empirical and animal laboratory studies, this study will address the question of whether Mingjing granule could contribute to improving efficacy, safety, and efficiency with need for fewer intravitreal injections of anti-VEGF, improving compliance and visual outcomes in the management of persons with nAMD.

**Trial registration:**

Chinese Clinical Trial Registry (http://www.chictr.org.cn), ChiCTR2000035990. Registered on 21 August 2020.

**Supplementary Information:**

The online version contains supplementary material available at 10.1186/s13063-021-05025-x.

## Background

Age-related macular degeneration (AMD) is a progressive, degenerative disorder that in the late stage causes a large scotoma in the central visual field that leads severe visual impairment and ultimately blindness. AMD accounts for 8.7% of all blindness worldwide and is the most common cause of blindness in developed countries, particularly in people older than 60 years. Its prevalence is likely to increase as a consequence of exponential population aging, and the projected number of people will increase to 288 million in 2040 [1]. In large Asian ethnic populations as in China, the incidence of AMD is also increasing. The Jiangning Eye Study, a population study in a local community of Shanghai showed that the prevalence of early AMD in persons aged 50 years or older was 9.5% and that of late AMD was 1.0% [2].

According to the new international consensus, AMD is defined into no obvious age-related changes, normal age-related changes, early AMD, intermediate AMD, and late AMD [3]. Late-stage AMD is further classified into two clinical forms: geographic atrophy and neovascular AMD (nAMD). nAMD is responsible for the most rapidly progressive form of AMD leading to central visual loss and will have an increasingly significant detrimental impact on quality of life among the elderly population [4, 5]. nAMD is characterized by the formation of choroidal neovascularization (CNV), the ingrowth of new blood vessels from the choriocapillaris through Bruch’s membrane into the subpigment epithelial or subretinal space [6]. Anti-VEGF agents are currently recommended as the first-line therapy for the treatment of nAMD when there is evidence of subfoveal neovascular lesions based on the notion of VEGF being a main driver of angiogenesis [7, 8]. Large multicenter randomized clinical trials have demonstrated regression of these lesions and subsequent improvement of central visual acuity in nAMD patients in a relative short term [9–12]. Although at present, the gold standard treatment for nAMD is anti-VEGF, this treatment requires repetitive intravitreal injections that carry the inherit risks of severe local adverse reactions and long term complications. Ocular inflammation, increased intraocular pressure, uveitis or less frequently endophthalmitis, retinal detachment, and retinal or vitreous hemorrhage are all serious ocular adverse events to anti-VEGF treatment [13, 14]. Others reported a lack (down to complete lack) of response with standard treatment patterns and even a decrease in treatment efficacy after repeated intravitreal injections [15].

From a public health perspective, the high cost of the anti-VEGF treatments is in conflict with the increasingly financially stressed health systems, setting reimbursement by payers as the major limiting factor. In middle- and low-income economies that do not offer employer public insurance schemes or subsidies, these treatments are often not accessible, and if they are, they must be paid out of pocket and thus contribute to increasing financial distress to patients and their families. A study from Singapore has estimated the economic burden of wet AMD in 2030 to be between 203.1 and 162.9 million US$ based a growth of 42% in the number of wet AMD cases by 2030 [16]. Furthermore, the burden associated with frequent clinic visit or individualized re-treatments by intravitreal injections over a long period of time for patients, caregivers, and physicians is significant and may lead to suboptimal outcomes because of adherence problems and underdosing [12, 17]. Large real-world studies demonstrated that nAMD patients generally lose vision within 2 to 5 years of diagnosis, despite anti-VEGF therapy [18]. Therefore, from an economic, patient management and public health perspective, there is an important unmet need to address potential alternative and complementary treatments to the current use of anti-VEGF in the management of nAMD [19].

In China, traditional Chinese medicine has been used to treat eye diseases for thousands of years. Although there was not a specific terminology for AMD in TCM classic books of ophthalmology, there were records of such kind of diseases described as metamorphopsia. Some candidate TCM formulas for AMD have been summarized through accumulated clinical experiences. Mingjing granule, a Chinese herbal compound composed of *Astmgali Radix (huangqi), Salviae Miltiorrhizae (danshen), Lycii Fructus (gouqizi), Ecliptae Herba (mohanlian), Cattail Pollen (puhuang), Cirsii Japonici Herba Carbonisata (daji)*, is developed from an empirical formula of a famous veteran ophthalmologist of TCM. Our previous in vitro studies demonstrated that Mingjing granule could protect human retinal pigment epithelium (hRPE) cell lines from apoptosis induced by blue light, and it could also enhance the phagocytosis of RPE cells at proper concentration [20, 21]. The animal studies showed that Mingjing granule had a certain inhibitory effect on CNV proliferation and could prevent CNV leakage. The mechanism may be related with down-regulating the level of VEGF, upregulating the level of pigment epithelium-derived factor (PEDF) and decreasing M2-like macrophages in the retina of Brown Norway (BN) rat model [22–25]. In addition, some studies have reported that bone marrow-derived cells (BMCs) not only participated in the composition of CNV cells, but also secreted some cytokines to affect the occurrence and development of CNV [26–30]. In our previous study, it was shown that Mingjing granule could inhibit the contribution of BMCs in the formation of CNV [31, 32]. Furthermore, several clinical studies have reported Mingjing granule could stabilize the vision loss or improve visual acuity of nAMD, decrease the subretinal fluid, and reduce the area of CNV leakage with no significant adverse events or laboratory abnormalities [33–37]. However, to date, no high quality clinical trials have been undertaken for Mingjing granule. In this study, we will examine the efficacy and safety of the Mingjing granule in the treatment of nAMD through a randomized, double-blind, placebo-controlled trial.

## Methods

### Trial design

This is a randomized, double-blind, placebo-controlled trial. Participants will be randomly allocated into two groups, the test group and the control group. Patients in the test group will receive Mingjing granule plus ranibizumab, while those in the control group will receive placebo with ranibizumab. All of them will be followed up every 4 weeks. Mingjing granule and placebo will be dispatched every 4 weeks until week 24; ranibizumab will be administered as needed after three consecutive monthly injections until week 48 (Figs. 1 and 2). The protocol is designed following the guidelines of the Consolidated Standards of Reporting Trials and Standard Protocol Items: Recommendations for Interventional Trials (SPIRIT) (see Additional file 1 SPIRIT 2013 checklist). The trial has been registered with the Chinese Clinical Trial Registry (ChiCTR2000035990, registered on 21 August 2020).

**Fig. 1 Fig1:**
[figure not shown]
Trial flow chart. nAMD, neovascular age-related macular degeneration

**Fig. 2 Fig2:**
[figure not shown]
Study schedule. BCVA, best-corrected visual acuity; CRT, central retinal thickness; PRN, pro re nata. Ranibizumab will be administered as needed after three consecutive monthly injections (3 + PRN)

### Trial setting

We will recruit 180 persons with diagnosed nAMD from six hospitals in China:
Foshan Hospital of Traditional Chinese Medicine,Shenzhen Traditional Chinese Medicine Hospital,Henan Province Hospital of Traditional Chinese Medicine/The Second Affiliated Hospital of Henan University of Chinese Medicine,The Second Affiliated Hospital of Liaoning University of Traditional Chinese Medicine,The Affiliated Hospital of Shandong University of Traditional Chinese Medicine/Shandong Province Hospital of Traditional Chinese Medicine,The first Teaching Hospital of Tianjin University of Traditional Chinese Medicine.

### Recruitment

For the recruitment of possible participants for the study, we will advertise using an information poster placed on notice boards in every participating center and resident communities. The information poster will include a brief description of the subjects that are eligible and details of activities and necessary contributions as participants in the study. For those people who are ineligible or decline to participate, we will record the basic demographic information and reasons for non-participation. The investigator will introduce the protocol as well as the benefits and risks to the enrolled participants and an informed consent form is mandatory before the study.

### Randomization and allocation concealment

Random sequence table will be generated by the Strategic Applications Software (SAS, version 9.4, SAS Institute, Inc., Cary, USA) and performed by the Institute of Clinical Pharmacology, China Academy of Chinese Medical Sciences. Participants will be allocated randomly into one of the two groups with a ratio of 1:1. The identification code and random number is unique for each participant.

### Blinding

All participants, clinical physicians, nurses, data managers, and statisticians and other staff will be blinded to the treatment allocations until the trial is completed. The placebo looks and tastes indistinguishable from Mingjing granule. The randomization list and blinding codes will be kept strictly confidential. Emergency unblinding process should only be done when the knowledge of intervention allocation is essential to guide the clinical management. The blinding will be broken after obtaining the consent of principle investigator.

#### Inclusion criteria

Exudative changes due to active CNV lesions secondary to AMD in one eye or both eyes.Aged 50 to 80 years.The best-corrected visual acuity (BCVA) between 73 and 34 assessed by early treatment diabetic retinopathy study (ETDRS) charts (approximately 20/40-20/200 Snellen equivalent).Agree to participate in the trial and provide written informed consent.

#### Exclusion criteria

Prior treatment of the study eye with intraocular anti-VEGF agents, verteporfin photodynamic therapy, other laser, corticosteroids, surgery (except cataract surgery at more than 30 days prior to screening) or systemic use of anti-VEGF products within 3 months prior to study entry.Ocular condition in the study eye that might impact vision and confound study outcomes.Active severe infection/intraocular inflammation in the study eye.Unclear dioptric media in the study eye that affecting fundus photography and optical coherence tomography (OCT) examination.Those with severe cardiovascular diseases, cerebrovascular diseases, impaired hepatic and renal function (aspartate transaminase/AST and/or alanine transaminase/ALT 2-fold the upper limitation of normal or above, the same for creatinine), hematopoietic diseases, or severe life-threatening primary diseases, mental illness (such as depression disorder, anxiety disorder).History of allergy to the study/treatment-related agents.Previous (within 3 months) or concomitant participation in another clinical study with investigational medicinal products.Patients who the investigators deem to be ineligible for the study.

#### Withdrawal criteria

In cases of worsening disease or concomitant complications with a necessity of safety evaluation and curative treatment.With the forbidden therapy and medication history during the trial, which will lead to bias for efficacy and safety evaluation.

### Interventions

#### Test group (Mingjing granule group)

Participants in the test group will be instructed to dissolve Mingjing granules (5.95 g/bag) in 200 ml hot water and take the solution orally twice a day for 24 weeks. Mingjing granule will be manufactured, packaged, and labeled by pharmaceutical factory (Beijing Tcmages Pharmaceutical Co. Ltd.). The main ingredients include *Astmgali Radix (huangqi), Salviae Miltiorrhizae (danshen), Lycii Fructus (gouqizi), Ecliptae Herba (mohanlian), Cattail Pollen (puhuang), and Cirsii Japonici Herba Carbonisata (daji)*.

